## Abstract

**Background:**

In recent years, routine outcome monitoring has been increasingly complemented by routine process monitoring in psychotherapy and other health care settings. Various approaches to therapy feedback exist, differing in assessment frequency, integration into the therapeutic process, and degree of personalization. In this study, we will use a procedure of high-frequency assessment through daily self-ratings, a standard process questionnaire, alongside a personalized questionnaire derived from case formulation, and frequent feedback interviews using visual diagrams to mirror the ongoing therapeutic processes.

**Objective:**

This study aims to investigate the effectiveness of combining routine process monitoring with hypno-psychotherapy (autosystemic hypnotherapy) by comparing it to autosystemic hypnotherapy without process feedback in the outpatient treatment of mood disorders. It also seeks to examine process-outcome relationships and mechanisms of change through high-frequency self-assessments and session-based feedback.

**Methods:**

This study is a randomized controlled trial with 2 arms, using within-therapist randomization (ABAB design) in outpatient psychotherapy. Participants are recruited offline via routine intake procedures. A total of 100 patients will be randomly assigned to one of the two conditions following a waiting period. The inclusion criterion is the existence of any mood disorder (major depressive disorder or anxiety disorder), assessed via a clinical interview. Each therapist treats patients in both conditions. Outcomes will be measured at 4 time points: after diagnosis confirmation, postwaiting period, posttreatment, and a 6-month follow-up. Primary and secondary outcomes, including symptom severity, will be assessed using questionnaires. Data collection also includes patient and therapist session evaluations using the Bern Patient and Therapist Session Questionnaire. In the feedback condition, therapists conduct frequent interviews using time-series data generated from daily self-assessments using the synergetic navigation system, including the Therapy Process Questionnaire and an individualized measure based on case conceptualization.

**Results:**

While this study is ongoing, the primary aim is to assess the effects of the feedback condition on therapeutic outcomes, including symptom reduction and patient motivation. This study will also explore how dynamic monitoring and feedback influence the therapeutic alliance and session-level improvements. It is expected that the feedback condition will lead to improvements in symptom severity and therapeutic engagement compared to the nonfeedback condition. Recruitment is ongoing, with 22 participants enrolled. The training of therapists and the data collection began in 2022. Data collection will end and study findings will be published in 2027. The German Society for Auto-Systemic Hypnotherapy is funding these training courses.

**Conclusions:**

This study combines effect and process measures within a feedback condition, compared to a nonfeedback condition. It incorporates dynamic process assessment to explore change mechanisms by analyzing patterns of time-series data and session ratings by patients and therapists. The approach provides insights into how continuous feedback and tailored monitoring influence therapeutic progress and outcomes.

**Trial Registration:**

OSF Registries osf.io/z2efy; https://doi.org/10.17605/OSF.IO/Z2EFY

**International Registered Report Identifier (IRRID):**

DERR1-10.2196/78166

## Introduction

### Effects of Therapy Monitoring and Feedback

For many years, monitoring and feedback procedures have been implemented in mental health care and in psychotherapy. Some researchers and practitioners identify these procedures as part of “good practice” [1] and even as the “most significant innovation in therapy practice within the past 20 years” [2]. Studies (case studies, implementation reports, and randomized controlled trials [RCTs]) tried to investigate the effects of monitoring and feedback in different mental health settings, applied to the treatment of many different diagnoses. Meta-analyses report small to medium overall effect sizes and showed that the feedback significantly reduces the odds of treatment dropout [3,4]. With respect to the effects, it has to be noted that the methodological quality of the studies is different and often poor [5], for example, pragmatic trials were realized with outcome assessments which were not independent of the process measures [6], and studies often are statistically underpowered (small, expected effect sizes require larger sample sizes) [7]. Other criteria concern the proof of using the feedback as intended—such as the manipulation check in an experiment—which, in case of not being taken for granted, may reduce the effect size of interventions compared to treatment as usual [8], and the implemented spectrum of outcome and progress measures [9].

To obtain a deeper insight into the mechanisms of feedback procedures, it should be considered that there are different approaches to realize it. Depending on the paradigmatic frame of the procedure, which can be linear and standardized or nonlinear [10,11], there may be different mechanisms of intervening and creating effects. The linear approach usually focuses on standard tracks or expected treatment responses [12], based on infrequent measures (eg, session by session). The nonlinear frame is based on the conceptualization of psychotherapy as a self-organizing and chaotic process [10,11] and does not presume any assumptions on the shape of trajectories [13]. Presuming standard tracks, pathways of clinical change are expected to run on these tracks, with deviations being at risk of deteriorations or unfavorable developments [14,15]. In case of “not on track” courses, clinical support tools are offered [16]. Different from this, nonlinear monitoring and feedback is based on more frequent and equidistant measures (eg, daily assessments) and, in consequence, on continuous feedback interviewing and process reflection (eg, in every session or every second session). Sampling rates with frequent and equidistant measures allow for different options of analyzing the pathways (time series) of change [17]. No specific incidents (eg, “not on track” states) are required for executing feedback talks. A focus of interest is on occurring critical instabilities, which are valued as precursors of upcoming pattern transitions [18].

Different from high-frequency process monitoring, the so-called routine outcome monitoring [19] focuses on outcome criteria, which are usually given by standard outcome questionnaires such as Outcome Questionnaire-45.2, Symptom Checklist-90-Revised, Depression Anxiety Stress Scales, or Beck Depression Inventory. The sampling rate is low, for example, each month or lower. In consequence, no real time series can be created. In contrast, the process monitoring approach as applied in this study includes a spectrum of common factors that have been proven to be important for creating successful treatments [20]. A Therapy Process Questionnaire (TPQ) was developed for daily self-assessments, which are not restricted to in-session evaluation but can be carried out in the real-world setting of the patients (eco-systemic approach). It includes factors as “well-being and positive emotions,” “emotional and problem intensity,” “motivation for change,” “insight/confidence/therapeutic progress,” and “mindfulness/self-care” [21].

Another difference exists between standardized and personalized procedures, with standardized approaches using predefined questionnaires, whereas personalized measures usually are based on case formulations as the idiographic system modeling and can be implemented by a questionnaire editor, as it is available in the synergetic navigation system (SNS) [22]. As practical experience shows, compliance rates can be optimized by personalized approaches of monitoring and feedback because they focus on patients’ own goals and topics [23]. The items of the questionnaires in use are created by the patients themselves, improving the experienced meaningfulness and thereby, the validity of the measures.

In consequence, there may be different mechanisms of creating effects and benefits by different approaches. Complex high-frequency procedures need intense training for the professionals, closer contact with the patients, a higher frequency of feedback sessions, and a higher degree of personal involvement of the patients, with corresponding effects on emotions, self-experience, and behavior by daily self-assessments (“measurement is intervention”). Clinicians also report on different attitudes to critical periods (instabilities) which are more desirable and less threatening if you see psychotherapy as a self-organizing process running through cascades of pattern transitions, and open-mindedness to different patterns of change. Other mechanisms may be more similar between different approaches, for example, that feedback may provide new information (though it may be various types of information that seem to be important), that feedback enhances patient-clinician communication (though it may focus on different topics), or that it may improve the therapeutic alliance [24]. Successful strategies of implementation into the respective setting of application, training procedures with different contents and messages concerning linear or nonlinear processes, and the clinician’s attitude toward the usefulness of the procedure seem to be important [4].

The research question of the study presented in this paper focuses on the effects of personalized high-frequency feedback based on case formulation (idiographic system modeling) in the context of a nonlinear dynamic systems approach combined with a hypno-psychotherapy called autosystemic hypnotherapy (ASH; original German term: Autosystemhypnose), compared with treatment as usual, in this case, ASH only.

### Hypnotherapy and the Concept of ASH

Hypnotherapy is an evidence-based treatment method that has gained increasing recognition in psychological and medical settings. Its effectiveness is particularly well established in the treatment of anxiety disorders (ADs): a meta-analysis of 17 studies (N=690) [25] reported medium to large effect sizes, showing that patients who received hypnosis for anxiety demonstrated a weighted mean effect size of 0.79 (95% CI 0.61-0.97) posttreatment, suggesting that the average hypnosis patient improved by more than 79% (based on Cohen *d* interpretation) compared to control participants. At follow-up (7 studies, N=215), the mean effect size was 0.99 (95% CI 0.74-1.24), reflecting an improvement greater than 84% of controls. Hypnotherapy has also proven highly effective for depression. In an RCT [26], hypnotherapy was found to be noninferior to cognitive behavioral therapy in treating mild to moderate depression. After 12 months, the response rate (defined as ≥50% symptom reduction) was 44.6% (33/74) of patients who responded to hypnotherapy (compared to 30/78, 38.5%, for cognitive behavioral therapy), indicating sustained therapeutic effects.

The therapeutic efficacy of hypnotherapy is based on its structured therapeutic process and its neurobiologically grounded mechanisms. Hypnotherapy typically follows four evidence-based phases [27]:

Prehypnotic preparation: therapist and patient explore beliefs, previous experiences, and treatment goals (eg, “reducing panic attacks from daily to ≤1 per week”) while clarifying misconceptions about hypnosis. This builds trust and aligns expectations.Hypnotic induction: using focusing techniques or verbal guidance, the therapist induces a state of focused and relaxed attention. Critical reasoning is bypassed, and a trance state is typically reached within 5-10 minutes.Therapeutic suggestions: this phase involves tailored therapeutic suggestions and metaphors designed to elicit emotional, psychological, or physiological changes aligned with the treatment goals. These use the brain’s heightened suggestibility during trance to reduce symptoms and promote adaptive experiences.Posthypnotic integration: before returning to normal awareness, patients receive posthypnotic suggestions to reinforce and integrate change into daily life. They are encouraged to apply trance-derived insights to real-world situations.

Recent neuroimaging research has provided compelling evidence that hypnosis induces distinct and measurable changes in brain activity. Using multimodal imaging, the research team [28] demonstrated that neural state changes occur synchronously with specific hypnotic induction instructions, indicating that hypnosis produces targeted modulations of brain function rather than nonspecific relaxation effects. In clinical populations, hypnosis has been shown to markedly inhibit the neural response of fear-related circuits, supporting its therapeutic efficacy in anxiety regulation:

Amygdala inhibition: functional magnetic resonance imaging studies show reduced activity in fear-processing centers during anxiety-focused hypnotherapy, correlating with symptom improvement.Suppression of the default mode network: trance reduces self-referential thought, helping patients disengage from rumination patterns.Enhanced top-down regulation: increased connectivity between prefrontal and limbic regions allows for improved cognitive restructuring of emotional responses.

This dual foundation—systematic procedural structure and targeted neuroplasticity—explains hypnotherapy’s superiority over placebo in meta-analyses [25,26] and supports its role as a method for modulating emotional and cognitive processes through attentional and self-regulatory mechanisms.

ASH [29] is a variant of hypnotherapy that integrates self-organizing systems theory and synergetic principles with classical hypnotherapeutic elements. As in traditional hypnotherapy, the therapist uses induction and suggestion, but ASH specifically addresses the client’s internal “autosystem” (self-regulatory system) and supports the development of self-observation and resource orientation. While ASH incorporates the established components of hypnotherapy (induction, suggestion, and integration), it adds additional distinctive features:

Diagnostic precision through hypnotic analysis: virtual “system scans” during trance enable the identification of unconscious blocks (eg, a patient visualizing their depression as “a black hole sucking away motivation” reveals implicit helplessness schemas), as well as exploration of the adaptive function of symptoms (eg, chronic pain maintaining caregiver attention).Resolution of multilayered resistances: the therapist guides the patient from addressing superficial objections (“therapy takes too long”) toward deeper levels of processing in which core conflicts (“if I recover, my partner will leave me”) are uncovered and reframed through trance-based cognitive restructuring.

While ASH has an established theoretical foundation and clinical tradition in German-speaking countries [30], no controlled efficacy studies exist to date. Accordingly, the present project aims to evaluate the effectiveness of ASH within a controlled design, building upon the broader evidence base for hypnotherapy.

### Major Depression and ADs

The planned study will apply feedback-informed psychotherapy in an outpatient setting to patients with major depressive disorder (MDD) and the spectrum of ADs, including MDD with anxiousness disorders. MDD is one of the most important mental health issues all over the world. It affects about 3.8% of the global population, or about 280 million people of all ages, with an increasing trend [31]. MDD is about 50% more common among women than among men. More than 700,000 people die due to depression-related suicide every year. MDD is characterized by a mental state of low mood and aversion to activity. It affects the thoughts, behavior, feelings, and sense of well-being of the person concerned. Experiences that would normally bring a person pleasure or joy give reduced pleasure or joy, and the afflicted person often experiences a loss of motivation or interest in many different activities. It may feature sadness, difficulty in thinking and concentration, or a significant increase or decrease in appetite and time spent sleeping. People experiencing MDD may have feelings of dejection or hopelessness and may experience suicidal thoughts. MDD is one of the most common comorbidities of many chronic diseases, including cancer and cardiovascular, metabolic, inflammatory, and neurological disorders. It is also a frequent comorbidity of other mental disorders, such as AD, borderline personality disorder, or obsessive-compulsive disorder. AD is the world’s most common mental disorder, affecting 301 million people in 2019 [32]. People with an AD may experience excessive fear or worry about a specific situation (for example, a panic attack or social situation) or, in the case of generalized anxiety disorder (GAD), about a broad range of everyday situations. They typically experience these symptoms over an extended period, at least several months. Usually, they avoid situations that make them anxious. Other symptoms of AD may include trouble concentrating or making decisions, feeling irritable, tense, or restless, experiencing nausea or abdominal distress, heart palpitations, sweating, trembling or shaking, trouble sleeping, or a sense of impending danger, panic, or doom. AD increases the risk for depression and substance use disorders, as well as the risk of suicidal thoughts and behaviors.

There are different kinds of AD, including GAD, characterized by persistent and excessive worry about daily activities or events, panic disorder, social AD, specific phobias, and others. Psychological mechanisms of GAD illustrate the comorbidity between anxiety and depression, for example, uncontrollable worry, constituting maladaptive strategies such as avoiding anxiety-related situations and emotional states. Individuals enduring GAD show deficits in detecting and regulating emotional states, which might accelerate a positive feedback loop between general stress symptoms and pathological worrying [33]. Experiential avoidance might lead to a restriction in proactive behavior because individuals will be focused on preventing negative events and maintaining safety [34].

### Therapist Effects in Randomized Clinical Trials

In this study, a randomized allocation of the treatment conditions will be realized among the therapists. Although blinded allocation of patients and health professionals is an important claim in double-blind randomized pharmacological trials, in evidence-based human interventions, for example, psychotherapy, health professionals cannot be blinded, because hopefully they are well-informed and fully aware of the interventions they apply [20,35]. This implies that personal preferences and the degree of identification with the treatment procedures that are conducted by the therapist (so-called allegiance effects) may affect the quality of the treatment as well as the outcome. However, therapist effects seem to be an important general (nonspecific) factor, which also will have consequences for the quality of processes and outcomes. Research on common factors revealed that therapist effects have bigger effects than treatment differences, in naturalistic designs, but even in RCTs, which usually are designed to minimize therapist effects (eg, by implementing treatment protocols) [20,36]. In consequence, crossed-therapist designs were suggested for naturalistic intervention studies [37,38], where a therapist is allocated to two or more treatment conditions, and therefore, potential differences in overall therapist effectiveness can be estimated across conditions. To estimate therapists’ personal treatment preferences, which may impact their effectiveness [8,39], these preferences should explicitly be assessed [20,38,40].

### Aims of This Study

This study addresses different research questions. There is some concern regarding the implementation of the procedure into the routine practice of outpatient psychotherapists, which is challenging because of the complexity of the routine process monitoring procedure. It encompasses an assessment of the patient’s personal resources, a case formulation, and, based on this, the development of a personalized process questionnaire. Regular feedback interviews during the sessions are scheduled with reference to the visualized results. Other research questions focus on the outcome of this study’s conditions and on the patterns of change that may characterize successful or unsuccessful therapies. Potential therapists’ implementation effects will be examined based on an ABAB therapist allocation (see the Study Design section). The main research questions are as follows:

Practicability: Can high-frequency process monitoring (daily self-assessments) and feedback interviewing (at least every second session) be implemented in outpatient routine psychotherapy, that is, in naturalistic settings? To what extent is the routine practice of outpatient psychotherapy supported by process monitoring? What can be learned from this study for the implementation of process monitoring into practice and training?Treatment outcomes: What is the efficacy of ASH compared with a waiting period control? What are the differences in the treatment efficacy of the two randomized implementation conditions, ASH versus ASH supported by personalized process monitoring and feedback in self-reported primary and secondary outcomes?Session effects and change dynamics: What are the differences between the implemented conditions in the experienced quality of the sessions (eg, micro-outcome) and in the therapeutic alliance? Does the process feedback support the therapeutic alliance? With reference to the time series created by the daily self-assessments: Are there specific features of the change dynamics (eg, discontinuous pattern transitions and critical instabilities) related to the outcome?Therapist effects: Are there any differences across therapists (therapist effects)? Is there an interaction between potential therapists’ preferences for a particular implementation condition and outcome?

## Methods

### Study Design

This study is designed as an RCT with 2 arms, using within-therapist randomization in the real-world clinical practice of routine outpatient psychotherapy in Germany.

Participants are recruited offline through routine intake procedures when presenting for outpatient psychotherapy with participating therapists. Patients who are suspected by the therapist to meet criteria for MDD, AD, or MDD with anxious disorders complex will be briefly screened for their ability and willingness to use a smartphone. If eligible, they will be informed about this study and its requirements by the respective therapist and asked whether they are interested in participating in a research project. Afterward, they will be informed of the procedure and the requirements of this study by the respective therapist. They obtain a flyer with basic information and, in case of concrete interest, will be instructed in detail and obtain an explanation to its full extent.

Patients who have consented to participate in this study will undergo a structured diagnostic interview (Structured Clinical Interview for *DSM-5* [*Diagnostic and Statistical Manual of Mental Disorders* {Fifth Edition}] – Clinician Version) [41] to confirm the inclusion criteria (diagnoses as listed in the Participants section, see below). The interview will be conducted remotely by an independent, trained clinical psychologist who is otherwise not involved in this study. The Structured Clinical Interview for *DSM-5* allows a final decision on including or excluding the patient. In addition to diagnostic confirmation, baseline information on participants’ current medication, concurrent treatment, and symptom severity will be systematically assessed. These variables will be considered as covariates in the main outcome analyses to account for potential prognostic influences. In addition, sensitivity analyses will be conducted to examine whether excluding participants with concurrent treatments or psychopharmacological medication changes affects the robustness of the findings. Following inclusion, a waiting period of 1 (minimum) to 6 months (maximum) begins for each patient, depending on the therapist’s capacity to initiate treatment.

After the waiting period, a randomization procedure decides on the allocation of a patient to condition A (ASH) or B (ASH+synergetic process management [SPM]). To ensure methodological rigor and internal validity, patients will be randomly assigned to one of the two treatment conditions using therapist-specific block randomization. The predefined block-randomized allocation sequences (eg, ABAB, BABA, AABB, BBAA, ABBA, and BAAB) will be generated in advance by the principal investigator for each therapist to ensure a balanced distribution of conditions within therapists. Patients will be assigned to intervention conditions in the order of study inclusion according to the next position in the respective therapist’s allocation sequence. The allocation sequence will remain concealed from the therapists until each new patient is assigned.

After the randomization, the treatment period starts, whose length depends on the concrete requirements of each patient and must be decided by the patient and therapist together (shared decision-making). In contrast to manualized treatments (adherence to protocol), this is a usual procedure in naturalistic settings. A follow-up assessment will be conducted 6 months after the end of therapy.

There are four assessment points: at the beginning of the waiting period (T1), at the start of the treatment (T2), at the end of the treatment (T3), and at follow-up (T4). The design of this study is illustrated in Figure 1.

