### Participants

As this study involves self-assessments via a smartphone application of the SNS, participants are required to have basic smartphone and internet literacy. This is assessed informally during the initial instruction and onboarding process by the respective therapist.

The patients who will be included in this study should be diagnosed with a spectrum of depression and ADs as listed in the *ICD-10* (*International Statistical Classification of Diseases, Tenth Revision*) [43], which is still valid in Germany. These are F32 depressive episode, F33 recurrent depressive disorder, F34 persistent mood disorders, F40 phobic ADs (eg, agoraphobia, social phobia, and specific phobias), F41 other ADs (eg, panic disorder, GAD, mixed anxiety and depressive disorder), F43 reaction to severe stress and adjustment disorders, and F45 somatoform disorders. At least one of these categories should be identified as the main diagnosis; other diagnoses (comorbidities) will be accepted. The reason for focusing on these diagnoses is their high prevalence rates and in consequently, the frequency of occurrence in routine outpatient psychotherapy. Exclusion criteria are aged younger than 18 years, acute suicidality, mental confusion, intoxication by drugs, substance use, and severe neurological diseases.

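### The covariates named for the main analyses are recorded 1 to 6 months before randomisation; the arm comparison needs T2 values, and no T2 record of medication or concurrent treatment is stated

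*Protocol article*

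**What the plan says.** All of the following is in the protocol article.

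- **Eligibility.** Under Study Design, the structured interview after consent "allows a final decision on including or excluding the patient".
- **Covariates.** In the same paragraph, "baseline information on participants’ current medication, concurrent treatment, and symptom severity will be systematically assessed". The next sentence fixes their use: "These variables will be considered as covariates in the main outcome analyses to account for potential prognostic influences".
- **Sensitivity analysis.** The plan will also examine whether "excluding participants with concurrent treatments or psychopharmacological medication changes affects the robustness of the findings". It gives no period over which a change counts.
- **Wait.** "Following inclusion, a waiting period of 1 (minimum) to 6 months (maximum) begins for each patient"; its length is set by when the therapist can take the patient on.
- **Allocation.** "After the waiting period, a randomization procedure decides on the allocation of a patient to condition A (ASH) or B" (ASH+SPM).
- **Exclusions.** Under Participants: "Exclusion criteria are aged younger than 18 years, acute suicidality, mental confusion, intoxication by drugs, substance use, and severe neurological diseases".
- **T2 data.** Assessments places all primary outcomes (the 14-item Symptom Checklist, SCL-14, and the DASS-21) and all secondary outcomes at T1 to T4, and adds a motivation questionnaire at T2. Medication and concurrent treatment are not listed there.
- **Analysis.** Statistical Analysis plans a repeated-measures ANOVA with condition as the between-subject factor and waiting (T1-T2) versus treatment (T2-T3) as the within-subject factor.

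**The concern.** The trial answers two outcome questions that have different baselines. The comparison of waiting with treatment starts at T1. The comparison of the two conditions starts when patients are randomised, at T2. The protocol names a single set of covariates, taken at the T1 end of the wait, for the main outcome analyses in general.

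Two things are at stake.

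1. **Arm comparison.** An old severity value predicts change after T2 less well than a value taken at T2. Medication and concurrent-treatment status may have changed in up to 6 months. The adjustment then recovers less precision than it could, and Power Considerations leaves little reserve: 98 patients are needed and 100 are planned.
2. **Waiting versus treatment.** This contrast is within patients and is not protected by randomisation. A drug or other therapy started during the wait alters T1-T2 change and, if continued, possibly T2-T3 change, while the named covariate still describes the patient at the interview.

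**Working it through.** **Step 1. Reproduce the plan's sample sizes.** Inputs from Power Considerations: f = 0.25 between conditions, f = 0.34 within subjects, correlation r = 0.50. There are two groups and m = 2 measurements. The article states no alpha; 0.05 is assumed.

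- Between: λ = f²·N·m / (1 + (m−1)r). At N = 98, λ = 0.0625 × 98 × 2 / 1.5 = 8.17, and power is 0.808. The smallest even N that reaches 0.80 is 98, as stated. At N = 100, power is 0.816.
- Within: λ = f²·N·m / (1−r). At N = 32, λ = 0.1156 × 32 × 2 / 0.5 = 14.80, and power is 0.961, matching the stated 96%.

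The plan's figures stand. What follows concerns the covariates only.

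**Step 2. Age of the covariates.** The order is interview, then a wait of 1 to 6 months, then randomisation. The interview values are therefore 1 to 6 months old at allocation.

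**Step 3. What T1 and T2 severity explain of T2-T3 change.** Assumptions: T1, T2 and T3 scores have equal variance (set to 1), every pair correlates at r = 0.50, and the severity recorded with the interview behaves like the T1 score.

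- Var(T3−T2) = 2 − 2r = 1.
- Cov(T1, T3−T2) = r − r = 0, so R² = 0.
- Cov(T2, T3−T2) = r − 1 = −0.50, so R² = 0.25 / 1 = 0.25.

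Adjusting for T1 severity leaves the residual variance at 1; adjusting for T2 severity leaves 0.75. The standard error is multiplied by √0.75 = 0.866. This is the precision that 100 / 0.75 = 133 patients would give without the adjustment.

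**Step 4. Sensitivity to r.** For T2 severity, R² = (1−r)² / (2−2r) = (1−r)/2, where r is the T2-T3 correlation. With assumed values of 0.30 and 0.70 the reduction is 35% and 15%. The zero for T1 requires the T1-T2 and T1-T3 correlations to be equal. If the T1-T3 correlation were 0.30 (assumed) and the others 0.50, Cov = −0.20 and R² = 0.04.

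**Step 5. Which contrast the figure belongs to.** The same assumptions give, for the two effects in the planned ANOVA if each level is a period change:

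- Group-by-period interaction, T3 − 2·T2 + T1: variance 6 + 2(0.5)(−2−2+1) = 3. T1 gives 0.5² / 3 = 0.083; T2 gives (−1)² / 3 = 0.333.
- Group main effect, (T3−T1)/2: T1 gives 0.25; T2 gives 0. This effect averages in the wait before randomisation, so it is not the arm difference over the treatment phase.

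With T1 and T2 both in the model, the residual variance of T2-T3 change is 1 − 2(0.25)/1.5 = 0.667. T1 severity therefore adds something beside T2, but does not replace it.

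**Step 6. Medication and concurrent treatment.** No figure can be derived. The article gives no rate of treatment started during the wait, and states no T2 record that would date it.

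**The case against.** The strongest reply is that T2 is already well served. The primary outcomes are measured there, the treatment phase in the ANOVA starts from the T2 score, and remission during the wait would be visible. This is right, and it rules out the reading that baseline status as a whole is not renewed at T2. What remains is that the severity value named as a covariate is the one recorded with the interview.

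Second, the planned sensitivity analysis presupposes that medication changes are recorded after the interview. A reader might infer that treatment started during the wait will be entered as none; the text does not support that. It does leave the period open. Changes before allocation cannot be affected by the arm and changes after it can, so pooling them mixes two different exclusions.

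Third, covariates measured before randomisation remain valid however old they are, and patients who remitted or began other treatment are balanced between arms in expectation. This stands: the arm comparison is not biased.

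Fourth, a reader might infer that patients who have become ineligible or have remitted are randomised, and that this dilutes the effect. The article describes no second check and calls the interview decision final, so the possibility is open. But it gives no rate, and a condensed article may leave such a check to the full protocol. Any power loss from dilution would rest on an invented proportion and would not be removed by changing covariates. Improvement during the wait is also the signal that the waiting comparison exists to capture.

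**Conclusion.** The point holds in a limited form. The stated covariates are outdated for the arm comparison, and no T2 record of medication or concurrent treatment is stated. The cost there is precision: under equal variances and equal correlations of 0.50, T1 severity explains none of the T2-T3 change variance and T2 severity about 25% (15% to 35% for assumed T2-T3 correlations of 0.70 to 0.30). The figure applies to contrasts that isolate the treatment phase. For the waiting-versus-treatment contrast the effect is possible confounding by treatment started during the wait, of unknown size. The documents do not support a claim of bias between arms or of a known share of ineligible or remitted patients. This is a worthwhile, inexpensive correction rather than a fault that endangers the trial.

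**What to change.** 1. Name the T2 SCL-14 and DASS-21 scores as the severity covariates for the arm comparison. T1 severity may stay in the model beside them. Since T2 is defined as the start of treatment, state that these scores are completed before allocation is revealed.
2. Repeat the medication and concurrent-treatment items at T2, also before allocation is revealed, and use those values as covariates for the arm comparison. Split the medication-change sensitivity analysis into changes during the wait and changes after randomisation.
3. Optionally, add a sensitivity analysis of the arm comparison without patients who are asymptomatic on the T2 scores, with the cut-off fixed in advance. This uses a status from before randomisation, so it keeps the randomised comparison intact.

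Separately, the sponsor should reconcile the final inclusion decision at the interview with randomisation 1 to 6 months later and with the exclusion criteria under Participants. No clinical rule is proposed here.

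The cost is a few items at an existing assessment point and a short amendment. At submission 22 of the planned 100 patients were enrolled; the article does not say how many had passed T2, and those may lack the new items.
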